
### Measures

#### *Background measures taken at initial assessment only*

Demographic information including age, marital status, ethnicity, socio-economic status, and education.

Lifetime of Experiences Questionnaire (LEQ) [18]. The LEQ assesses the extent of complex mental activity undertaken across the lifespan. It is a 42-item scale with a mix of 5-point Likert scale and free responses which are coded into ordinal scale scores according to structured scoring principles. The LEQ asks about participation in educational, occupational and cognitively-stimulating lifestyle activities during young adulthood, mid-life and later life, and about engagement in mental activities that are not specific to a given life-stage.

## Measures taken at initial assessment and 12 month follow-up

### Primary outcomes

Florida Cognitive Activities Scale (FCAS) [19]. The FCAS is a 25-item scale examining the degree of current participation in a range of cognitively-stimulating activities. Participation in each activity is rated on a 6-point scale from 0 (have never done this activity/have not done this activity in the past year) to 4 (do this activity every day). Possible scores range from 0 to 100 with higher scores indicating greater involvement in activities. The total score will represent the primary outcome. Two subscale scores can also be calculated to provide additional information. The Higher Cognition subscale contains 10 items relating to engagement in cognitively challenging activities, with possible scores ranging from 0 to 40. The Frequent Activities subscale contains eight items describing everyday tasks or activities, with possible scores ranging from 0 to 32. We will use the FCAS to assess participation in CA during the previous month.

Physical Activities Scale for the Elderly (PASE) [20]. This 10-item scale investigates frequency of participation in a range of physical activities including sedentary activities, walking, light, moderate, or strenuous sport or recreational activities, strength and endurance exercises, light or heavy housework, home repairs or gardening, and caregiving, and the physical demands of any work undertaken for pay or as a volunteer. Response formats are three-point (seldom, sometimes, often) or four- point (<1 h, 1–2 h, 2–4 h, >4 h) scales or categorical (yes/no) responses. The total PASE score is computed by multiplying the amount of time spent in each activity (hours/week) or participation (yes/no) in an activity by the empirically derived item weights presented in [20] and summing over all activities. A higher total score indicates greater levels of activity.

### Secondary outcomes

#### *Assessment of psychosocial factors*

General Self-Efficacy Scale (GSES) [21]. This 10-item scale assessing self-efficacy presents a series of statements which the respondent rates on a 4-point scale to indicate how accurately the given statement describes him/her from 1 (not at all true) to 4 (completely true). Possible scores range from 1 to 40 with higher scores indicating higher perceived self-efficacy.

Center for Epidemiologic Studies Depression Scale (CES-D) [22]. This 20-item scale presents a list of feelings or behaviors and asks the respondent to rate the extent to which they felt or behaved this way during the past week on a 4-point Likert scale from 0 (rarely or none of the time) to 3 (most or all of the time). Possible scores range from 0 to 60 with higher scores indicating more signs of depression.

CASP-19 [23]. This 19-item scale assessing quality of life in older people is based on a needs satisfaction model and items relate to the four domains of control, autonomy, self-realization, and pleasure. Responses are scored on a four-point scale from 0 (never) to 3 (often). Possible scores range from 0 to 57 and higher scores indicate better perceived quality of life.

Social networks, social support, and social engagement: participants are asked about their frequency of contact with others including family and friends, about the quality of social relationships (rated on a scale from ‘very close’ to ‘not at all close’) and about their level and frequency of societal involvement including social and political engagement, participation in social recreational activities, cultural activities and leisure time such as holidays and trips. Items were taken from the English Longitudinal Study of Ageing [24]. With regard to social networks, people are considered disadvantaged if they do not live with a partner and do not meet any of their children, family or friends at least three times a week. With regard to social support, people are considered disadvantaged if they have no-one (partner, children, family, or friends) strongly supporting them. With regard to social engagement, a person is classified as ‘socially detached’ if there is disadvantage on three of six indicators of social participation: social networks, social support, social/political involvement, and participation in cultural, recreational, and leisure activities.

#### *Cognitive assessment*

Montreal Cognitive Assessment (MOCA) [25]. The MOCA is a brief cognitive screening test covering the domains of immediate and delayed recall, attention, executive function, visuospatial processing, language and naming, abstraction, and orientation. The total score can be corrected for level of education. A score of 26 or more out of 30 suggests no difficulties with cognitive function.

California Verbal Learning Test (CVLT-II) [26]. A list of words is read and the participant is asked to say all that s/he can remember. The same list is read, and recall elicited, four more times (five trials altogether). After trial 5 recall, a different list is read and the participant is asked to say all that s/he can remember. Then short-delay free recall of the first list is requested. After a 20 min delay (during which other tasks can be undertaken) long-delay free recall of the first list is tested. The total immediate recall score for List A trials 1 to 5 and the long-delay free recall score are the scores to be taken for this study.

Delis-Kaplan Executive Function System [27]. In this study we will use two of the d-KEFS subtests, Trail Making and Verbal Fluency. Trail Making is a timed visual-motor task assessing flexibility in thinking. The participant is first asked to draw a line connecting numbers spread randomly on the sheet of paper in ascending order. Next, the participant is asked to draw a line connecting numbers and letters in an alternating manner, with numbers in ascending order and letters in alphabetical order (1 - A - 2 - B - 3 and so on). The score to be used in this study is the time taken to complete the second task minus the time taken to complete the second task, in seconds. Verbal Fluency is a task assessing the ability to produce words according to a given set of rules and within a time limit. The participant is asked to produce as many different words as possible beginning with the letters f, a, and s. One minute is allowed for each letter. There should be no proper nouns or repetitions. The score is the total number of correct words summed across the three letters. Scaled scores can also be calculated.

#### *Physical fitness, health, and dietary assessment*

Health assessment covering medical history, anthropometric data, medication use, and blood pressure. A blood sample will be taken for lipid profile, to give a QRISK2 score [28]. This multifactorial score gives a percentage risk for cardiovascular disease over a 10-year period. The QRISK2 has been independently validated [29] and is based on data specific to the UK allowing for differing ethnicity and using postcodes to account for deprivation. The aim is to identify asymptomatic people without established cardiovascular disease (CVD) but who have a combination of risk factors which puts them at high total risk (estimated CVD risk ≥ 20% over 10 years) of developing atherosclerotic CVD for the first time. Blood samples will be analyzed by independent National Health Service laboratory staff. The blood results are copied to the participant’s primary care physician and also screened by [name]. Health needs (for example, regarding cardiovascular risk reduction) will be identified and details will be available to support the goal-setting interview process. If screening indicates a need for urgent medical attention in the view of the physician ([name]), an appropriate referral will be made.

Senior Fitness Test (SFT) [30]. Several brief subtests from the SFT will be used, involving common activities such as getting up from a chair, walking, lifting, bending, and stretching. These provide an assessment of upper and lower body strength, flexibility, and agility.

Physical fitness will be evaluated by determining predicted aerobic capacity from a submaximal graded exercise step test [31].

Mediterranean Diet Adherence Screener (MEDAS) [32]. This 14 item questionnaire examines participants’ adherence to a typical Mediterranean diet in terms of food intake habits and the frequency of consumption of foods such as olive oil and pulses. Adherence to this type of diet has been related to better physical and mental health outcomes [33].

#### *Process measures*

Data on attendance at the Centre and participation in Centre activities will be examined for participants in all three groups.

For groups 2 and 3, changes in goal performance and satisfaction ratings, and the extent of goal attainment, will be assessed.

### Measures for evaluation of cost-effectiveness

EQ-5day [34]. The EQ-5day is a standardized measure of health status and health outcome, applicable to a wide range of health conditions. In the first section, the respondent is asked to select one of three options for each of five dimensions: mobility, self-care, usual activities, pain/discomfort, and anxiety/depression. For each dimension, the three response options are coded on a 3-point scale from 1 (no problems) to 3 (unable to perform/extreme problem). This yields a descriptive profile of scores across the five dimensions. The second part of the measure is a visual analogue scale for self-rating of health-related quality of life (‘your health state today’).

ICECAP-O [35,36]. The ICECAP-O (ICEpop CAPability measure for Older people; ICEpop refers to Investigating Choice Experiments for the Preferences of Older People; http://www.epi.bris.ac.uk/research/programmes/icepop.htm) is a brief 5-item quality of life measure for older people, conceptually linked to the capability approach whereby wellbeing is defined in terms of an individual’s ability to ‘do’ and ‘be’ the things that are important in life. The five items, covering the attributes of attachment, security, role, enjoyment, and control, are each scored on a 4-point scale. Possible total scores range from 5 to 20 with higher scores indicating better perceived quality of life.

Client Services Receipt Inventory (CSRI) [37]. The CSRI asks respondents about their use of health and social care services. At initial assessment the focus will be on service use in the preceding 3 months. At follow-up the focus will be on service use over the past 12 months. The questions cover contact with a range of health and social care professionals, prescription of medications, hospital appointments and stays, participation in local authority funded activities such as day centers, and participation in activities run by voluntary organizations (other than the AgeWell Centre).

### Qualitative inquiry

In-depth qualitative interviews with a sub-sample of participants from all three conditions (target *n* = 25) will examine sociobiographical influences on processes of change.

### Procedure

Individuals attending the Centre will be given information about the study and invited to consider participating in the trial by a member of the research team, after which they will be given as much time as they need to decide whether they wish to take part. Those who consent to participate will complete the baseline assessment in two face-to-face sessions with a researcher, one focusing on psychological, social and cognitive measures and lasting approximately 1.5 h, and the other focusing on physical health and fitness and lasting approximately 1 h. The researcher will then trigger the randomization. Participants will be allocated to one of the three conditions and will engage in the interview conducted according to the protocol for their allocated condition. Those in the goal-setting with mentoring group will have bi-monthly mentoring phone calls from the interviewer over the following 12 months while the remainder will have no such contact. After 12 months all participants will engage in a follow-up interview in accordance with the condition to which they were allocated; for participants in the goal-setting and goal-setting with mentoring groups the interviewer will use the Bangor Goal-setting Interview to elicit current ratings of performance and satisfaction with performance for the originally-identified goals, while those in the control group will have a general discussion with the interviewer. The interviewer will then trigger the follow-up assessment and all participants will be reassessed by blinded members of the research team.

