3. Group 3, goal-setting with mentoring, will receive the same interview as Group 2 plus a follow-up mentoring phone call from the interviewer after 1 month (in month 2 of participation in the study) and then bi-monthly thereafter (in months 4, 6, 8, and 10) to review progress, problem-solve regarding any obstacles to progress, encourage and reinforce successes, and support maintenance of change. Each participant will remain in the study for 12 months, and will engage according to personal choice in center and related activities. Attendance and activity participation will be recorded. All participants will be reassessed after 12 months by a researcher blind to group allocation. At follow-up assessment, participants will re-rate performance and satisfaction with regard to each identified goal, and a rating of goal attainment will be made.

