The Bangor Goal-Setting Interview, developed by the research team, provides a structured format for the goal-setting process. This interview is similar in some respects to the format of the Canadian Occupational Performance Measure [14], a well-established clinical method for measuring performance in a standardized manner across different individual goals [15], which has proved to be a sensitive measure of change in previous rehabilitation research [16]. However, it derives from a different theoretical model, incorporates a number of different features, and has been developed primarily as a research tool. The Bangor Goal-Setting Interview is based on the social cognitive theory of behavior change [10] and on the concept of motivational interviewing [17]. The interview structure allows researchers to select areas of behavior that are relevant to the aims of the study; for the present study we have selected the four areas of physical activity, cognitive activity, diet and health, and social engagement. The interview proceeds in three stages. Firstly, each of these areas is discussed in turn with a view to eliciting issues that might form the basis for behavioral goal-setting. For each area, the participant rates perceived importance of making changes in this area, and readiness to make changes in this area, on a scale of 1 to 10 (where 1 is not at all important/not at all ready and 10 is extremely important/completely ready). Once all areas have been discussed, the second stage involves revisiting each area in turn and negotiating specific behavioral goals that conform to SMART principles (specific, measurable, achievable, realistic, and time-delineated). For this study, we specified that two to five goals should be set, and that these could be in any of the four areas covered. Once a goal is set, and current performance described, possible barriers and facilitators to achieving the goal are discussed using specific prompts, with an emphasis on identifying the resources available to support behavioral change. Additionally, goal attainment indicators are specified, providing clear descriptors of what would constitute 25%, 50%, and 75% goal attainment. In the final stage of the interview, the participant is asked to rate, for each of the goals that have been identified, current performance and satisfaction with performance on a scale of 1 to 10 (where 1 is unable to perform/extremely dissatisfied and 10 is able to perform perfectly/extremely satisfied). Mean scores for performance and satisfaction with performance across goals are calculated by dividing in each case the sum of the scores for all goals identified by the number of goals set. At follow-up, the participant re-rates current performance and satisfaction with performance for each goal so that changes in ratings can be examined. The interviewer elicits information about current performance and uses the previously-specified goal attainment indicators to determine the extent of progress towards achieving the goal. Within the interview schedule there is scope to elicit informant ratings of performance and descriptions of goal attainment, for comparison purposes; this is particularly relevant for example where respondents have cognitive impairments. Similarly, assessor ratings can be made where the assessor has been involved in a therapeutic or supportive capacity in helping the participant work towards selected goals. As the present study involves healthy older participants, only self-ratings will be elicited.

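### The 12-month goal-review interview, which only the goal-setting arms receive, precedes the participant-reported primary outcomes and adds an avoidable risk of differential reporting

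*Protocol article*

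**What the plan says.** The Procedure section of the protocol article sets the 12-month sequence. It begins with an interview tied to allocation: "After 12 months all participants will engage in a follow-up interview in accordance with the condition to which they were allocated". For Groups 2 and 3 this is a goal review, in which "the interviewer will use the Bangor Goal-setting Interview to elicit current ratings of performance and satisfaction with performance for the originally-identified goals". Group 1 has no such review at this point. The outcome assessment comes next: "The interviewer will then trigger the follow-up assessment and all participants will be reassessed by blinded members of the research team". How long after the interview it takes place is not stated.

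The Intervention section describes what the goal review contains: "The interviewer elicits information about current performance and uses the previously-specified goal attainment indicators to determine the extent of progress towards achieving the goal". On the choice of goals, "we specified that two to five goals should be set, and that these could be in any of the four areas covered"; the four areas are physical activity, cognitive activity, diet and health, and social engagement. The Group 3 paragraph of the same section also mentions the re-rating: "At follow-up assessment, participants will re-rate performance and satisfaction with regard to each identified goal, and a rating of goal attainment will be made".

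Under Primary outcomes, FCAS and PASE are both scales of how often the participant takes part in activities. For the FCAS, "We will use the FCAS to assess participation in CA during the previous month". The Data analysis section plans an ANCOVA on follow-up scores adjusted for baseline, with two contrasts: Group 1 against Groups 2 and 3 combined, and Group 2 against Group 3. Blinding is stated for the follow-up assessor only.

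**The concern.** The answers to FCAS and PASE come from the participant. Someone who has just been asked how far they have progressed on a walking goal or a computing goal may answer later questions about walking or computing differently from someone who has had a general conversation. They may wish to be consistent with what they told the interviewer, or recall may have been refreshed. Blinding the assessor does not address this, because the assessor does not generate the answer. Adjusting for baseline does not address it either, because no 12-month goal review precedes the baseline measurement.

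A participant who has recently reviewed goals is also more likely to mention them, and so to reveal the allocation to the assessor.

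The review is confined to Groups 2 and 3, so any resulting shift is confounded with allocation in the contrast that asks whether goal-setting works. The Data analysis section says the results will supply effect sizes and variability for a definitive trial. A shift would pass into that effect size whatever the significance test showed.

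**Working it through.** **Step 1. Order and content, by arm.**

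| Step at 12 months (Procedure) | Group 1 | Groups 2 and 3 |
|---|---|---|
| First: interview | General discussion | Re-rating of own goals |
| Then: triggered by the interviewer | Blinded reassessment, with FCAS and PASE | Blinded reassessment, with FCAS and PASE |

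Nothing elsewhere in the article places FCAS or PASE before the interview. The Group 3 paragraph under Intervention puts the re-rating at the follow-up assessment, but gives no order relative to the scales and names no rater. It is looser than the Procedure section and does not contradict it.

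**Step 2. Which contrast is exposed.** Let *b* be an order-related reporting shift, in SD units, common to Groups 2 and 3 and absent from Group 1.
- Group 1 versus the mean of Groups 2 and 3: bias = (b + b)/2 − 0 = b.
- Group 2 versus Group 3: bias = b − b = 0.

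**Step 3. Illustration of size.** The document's own figure reproduces: 3 arms × 25 = 75 (Participants section). That number rests on expected attendance, so there is no power calculation to check.

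From the document: 25 per arm, ANCOVA with baseline as covariate. Assumed, because the document does not give them: two-sided 5% level, all 75 analysed, no true effect, baseline to follow-up correlation r, and the shift b.

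- Standard error in SD units: SE = √[(1/25 + 1/50)(1 − r²)]. At r = 0.6, SE = √(0.06 × 0.64) = 0.196.
- Degrees of freedom: 75 − 3 group means − 1 covariate = 71.
- Rejection rate: two-sided probability from a non-central t with non-centrality b/SE.

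| Assumed b (SD) | b/SE at r = 0.6 | Rejection, r = 0.6 | Rejection, r = 0.5 to 0.7 |
|---|---|---|---|
| 0 | 0 | 5% | 5% |
| 0.1 | 0.51 | 8% | 8% to 9% |
| 0.2 | 1.02 | 17% | 15% to 20% |
| 0.3 | 1.53 | 33% | 29% to 39% |

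At r = 0 the rates for 0.2 and 0.3 SD are about 13% and 23%. The table shows what a given shift would do. It is no evidence that a shift of any particular size exists.

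**The case against.** Several objections are sound and limit the point.

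- **The interval is unknown.** The text says only that the interviewer then triggers the assessment. A reader might infer that participants come straight from the goal review to the questionnaires, but the gap could be hours or weeks. Any carry-over depends on it.
- **The direction is unknown.** A reader might infer that the shift must favour the hypothesis. Reviewing goals against indicators fixed in advance could instead make reporting more accurate, or lower it where goals were missed. Some participants may also have goals only in diet and health or social engagement.
- **Order is only part of the problem.** Participants know which interview they had, and Groups 2 and 3 left theirs with a written action plan. General desirability bias remains in any order. The proposed change removes only the increment due to order, and the illustration applies to that increment alone.
- **This is a feasibility study.** No significance level or decision rule is stated, so false-positive rates are a secondary way to express the risk. Bias in the effect size carried forward is the more relevant consequence.
- **Less exposed measures exist.** Attendance records, the Senior Fitness Test, the step test and QRISK2 allow a partial check, although they do not repair FCAS or PASE.

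Three stronger readings are not supported. The Intervention and Procedure sections do not contradict each other on the re-rating, as Step 1 of the check shows. A missed interview is not said to block assessment: the text gives a sequence and says that all participants are reassessed. And the text does suggest that whoever conducts the interview and the mentoring calls also judges attainment in Group 3, but attainment is listed as a process measure and no Group 2 versus Group 3 test of it is planned, so this does not bear on the primary outcomes.

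None of these objections changes the stated order, or the fact that only two of the three arms review goals before reporting activity.

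**Conclusion.** The point holds as an avoidable design weakness that is cheap to correct. The order and the difference in content between arms are explicit in the Procedure section. That the order shifts the answers is a reasoned risk. The document neither states nor quantifies it, and its size and direction are unknown.

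The exposure is confined to Group 1 versus Groups 2 and 3 combined, and to the effect size from that contrast. A shift common to Groups 2 and 3 cancels in the other contrast. Under the assumptions listed, a shift of 0.1 to 0.3 SD due to order would raise the false-positive rate from 5% to between about 8% and 33% at a correlation of 0.6, and would bias the estimate by the same 0.1 to 0.3 SD. Neither assessor blinding nor baseline adjustment removes it.

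**What to change.** In the Procedure section, trigger the blinded 12-month assessment by date since randomisation and not by the interviewer. State that it is completed, at least for FCAS and PASE, before the 12-month goal-review or control interview. Reword the Group 3 paragraph of the Intervention section to match, so that both places give the same order.

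The cost is rescheduling. Recruitment began on 2 January 2012 (Trial status), so the first 12-month follow-ups fall due about January 2013, and a change made before then covers every participant. Sample size, measures and analysis model stay as they are. One small downside is that the activity questionnaires would then come before the goal re-ratings and could influence them. Those ratings are process measures, so this is the better place to accept an order effect.
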